**Methods:**

We have designed a multi-centre, parallel-group, non-inferiority randomized controlled trial to test the utility of non-targeted biopsies as an adjunct to colonoscopy surveillance for neoplasia detection in persons with inflammatory bowel disease involving the colorectum in routine clinical practice. Participants are randomized 1:1, stratified by study site, to either standard of care high-definition white-light colonoscopy with 32 to 40 non-targeted biopsies of non-neoplastic-appearing mucosa along with a sampling of abnormal-appearing mucosa (control group) or modified colonoscopy with targeted sampling alone (intervention group). The primary outcome for the full trial will be the proportion of persons with ≥ 1 neoplastic focus detected during colonoscopy. For the pilot phase, we will assess the feasibility of recruiting a minimum of 15% of the estimated sample size within 1 year, under identical conditions as the full trial, while maintaining ≥ 90–95% rate of protocol adherence and data capture. These participants will contribute data to the full trial. The trial is being conducted at 12 centres across Canada, with a total sample size of 1952 persons.

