## Trial design and conduct

This is a multi-centre, parallel-group, non-inferiority RCT. Participants meeting the eligibility criteria will be randomly allocated to one of the two groups, stratified by study site, using a web-based central randomization scheme coordinated by the Ottawa Methods Centre:Control group—standard of care screening/surveillance colonoscopy, with 32–40 interval non-targeted biopsies of non-neoplastic-appearing mucosa, as well as targeted biopsies or endoscopic resection of suspicious visible mucosal abnormalitiesIntervention group—modified screening/surveillance, with targeted biopsies or endoscopic resection of suspicious visible mucosal abnormalities alone

Randomization will occur intra-procedurally, once all clinical and endoscopic eligibility criteria have been confirmed. Study investigators and/or their trained research assistants will perform the following tasks: (i) assess study eligibility and obtain informed consent from patients; (ii) directly observe the study-related colonoscopy (trained assistant), to confirm intra-procedural eligibility criteria, randomize patients, ensure colonoscopy protocol adherence and obtain procedure-related information pertinent for the trial; (iii) perform medical record review, to collect historical and post-procedural data, including histology of biopsy/resection samples; (iv) conduct a virtual interview with patients a minimum of 2 weeks following the study colonoscopy, to ascertain procedure-related adverse events; (v) record all study-related data in a web-based case report form (developed by the Ottawa Methods Centre); and (vi) facilitate transfer of de-identified physical or electronic slide sets from patients with neoplasia/dysplasia for central adjudication.

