### Future trial outcomes

The primary outcome is the proportion of persons with ≥ 1 neoplastic focus in the colorectum.

The following are the secondary outcomes:(i)The mean and median number of neoplastic lesions per person(ii)The rate of advanced neoplasia (any of CRC, high-grade neoplasia, large neoplasia (> 2 cm diameter) or multifocal neoplasia (≥ 3 independent neoplastic foci throughout the colorectum))(iii)The neoplasia yield of non-targeted biopsies(iv)The mean and median number of tissue samples per person(v)The mean and median procedure time(vi)Rate of serious adverse events (SAE) within 2 weeks of colonoscopy [69] (hospital admission, bowel perforation, severe rectal bleeding requiring blood transfusion and/or repeat colonoscopy, acute cardiac or respiratory compromise or death)(vii)Proportion of persons referred for colectomy based on neoplastic findings(viii)The mean and median time to the next recommended surveillance examination(ix)Incidence of CRC over 5 years following study colonoscopy (obtained through linkage of patient data to provincial cancer registries or direct patient contact, at least 5 years following study completion)

We will conduct exploratory sub-group analyses of the primary outcome and multiple secondary outcomes based on disease type (CD vs UC), disease duration and prior biologic exposure.

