## Sample size calculation

The estimated sample size to assess non-inferiority of the intervention in the full trial is 1952 persons (976 per group), based on a 1-sided significance level of 2.5% and 80% power, assuming neoplasia detection rates of 15% and 14.5% in our control and intervention groups, respectively, and a non-inferiority margin of 5%. Our sample size estimate for the pilot phase (≥ 15% of the study sample size recruited within 1 year of study initiation) is guided by the feasibility of completing the full trial within an acceptable time frame of 5 to 7 years.

Our estimates for neoplasia yield in the 2 groups were guided by pooled analyses of clinical trials and observational cohorts conducted by the SCENIC consortium [50]. The pooled estimate from 4 studies (382 patients) of HD-WLE with non-targeted and targeted sampling was 17%, while the pooled estimate from 7 studies (1289 patients) of DCE (an alternative detection method to non-targeted sampling) was 13.6% [50]. A reasonable estimate for neoplasia detection rate in the control group is thus 15%. The pooled estimates for the proportion of persons diagnosed with neoplasia in non-targeted biopsies alone in these analyses ranged from 1.2% (in studies using DCE) to 1.5% (in studies using HD-WLE). However, we anticipated that these would be overestimates of the difference that would be observed in a present-day RCT, given continued improvements in IBD treatments, endoscope technology and colonoscopy practice quality, as well as a propensity towards closer inspection for visible lesions in the absence of non-targeted biopsies [28, 57]. Therefore, we estimated a 0.5% reduction in the neoplasia detection rate without non-targeted biopsies for this trial.

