## Data analysis

We will evaluate the pilot study results based on participant recruitment rate, protocol adherence and quality of data capture. Treatment allocation will remain concealed to study investigators following the completion of the pilot phase so as to not influence ongoing study recruitment. We require a minimum of 292 participants (> 15% of the full trial sample) to be recruited within 1 year of trial initiation at each site to deem adequate feasibility of recruitment for the full trial. We will accept up to a 5% rate of major protocol violations, up to a 1% miss rate of major variables and up to a 5% LFU amongst study participants recruited during the pilot phase. If these metrics are met and there are no safety concerns with the study intervention based on the Data and Safety Monitoring Committee (DSMC) review, we will proceed with recruitment to the full trial.

The full trial results will be assessed by per-protocol analysis and intent-to-treat (ITT) analyses. The chi-square test will be used to analyze the differences in binary categorical outcomes, and Student’s *t*-test will be used to analyze the differences in continuous outcomes. Non-inferiority of the primary outcome (proportion of persons with neoplasia detected) will be demonstrated if the upper limit of a one-sided 97.5% confidence interval around the expected true difference of 0.5% in favour of the control group (15% vs 14.5%) excludes a difference of more than 5%. If the baseline characteristics potentially influencing event rates have a standardized difference of ≥ 0.1, multivariable analysis will be further conducted.

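### Randomization is stratified by site, but the stated analysis has no site term, and covariate adjustment depends on a chance-imbalance trigger

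*Protocol article*

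**What the plan says.** Under Trial design and conduct, participants are "randomly allocated to one of the two groups, stratified by study site, using a web-based central randomization scheme". The abstract gives the ratio as 1:1 and the scale: "The trial is being conducted at 12 centres across Canada, with a total sample size of 1952 persons".

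The primary outcome for the full trial is binary (Future trial outcomes: "The primary outcome is the proportion of persons with" at least one neoplastic focus). The Data analysis section makes three statements that bear on it:

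- A test for binary outcomes in general: "The chi-square test will be used to analyze the differences in binary categorical outcomes".
- A decision rule for the primary outcome: non-inferiority is shown if the upper limit of a one-sided 97.5% confidence interval for the difference excludes more than 5 percentage points.
- A conditional adjustment: "If the baseline characteristics potentially influencing event rates have a standardized difference" of 0.1 or more, a multivariable analysis is carried out in addition.

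Site appears in none of the three. The article names no covariates for the conditional analysis and does not say how its result relates to the decision rule.

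**The concern.** Two features sit badly together. Site was judged important enough to be the only stratification factor, but the analysis as written does not use it. When randomization is balanced within sites, a standard error that ignores site includes between-site variation that the design has already removed from the comparison.

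Second, adjustment depends on observed imbalance. In a correctly randomized trial, imbalance is chance and says nothing about whether a covariate predicts neoplasia. A strong predictor that happens to balance brings in no adjustment, while a weak one that happens to differ does. The precision that adjustment offers comes from prognostic strength, so the rule selects on the wrong property.

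At stake are some unused precision and a supporting analysis whose existence is settled only after the data are seen. The validity of the main comparison is not at stake.

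**Working it through.** **Inputs from the article.** Rates of 15% (control) and 14.5% (intervention), margin 5 points, 976 per group, "based on a 1-sided significance level of 2.5% and 80% power" (Sample size calculation); 12 sites (abstract); trigger 0.1 (Data analysis).

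**1. Reproduce the sample size.**
Variance term: 0.15×0.85 + 0.145×0.855 = 0.2515.
n per group = (1.960 + 0.842)² × 0.2515 / (0.05 − 0.005)² = 974.7, so 975, against 976 stated.
At 976 per group, SE = √(0.2515/976) = 0.01605 and power = Φ(0.045/0.01605 − 1.960) = 80.05%.
The stated size therefore matches a plain two-proportion comparison with no site term.

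**2. How often chance reaches the trigger.**
SD of a standardized difference = √(2/976) = 0.0453.
P(|d| ≥ 0.1) = 2 × [1 − Φ(0.1/0.0453)] = 2 × [1 − Φ(2.209)] = 2.7% per covariate.
For at least one of m independent covariates, 1 − (1 − 0.0272)^m. The article gives no covariate count, so m is an assumption:

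| m | P(at least one reaches 0.1) |
|---|---|
| 5 | 13% |
| 10 | 24% |
| 15 | 34% |
| 20 | 42% |

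**3. What leaving out site costs.** With equal allocation within each site, the stratified and crude risk differences coincide, and only the standard error changes. The share of variance removed is about (between-site SD)² / (0.15×0.85). A between-site SD of 5 points gives 0.0025/0.1275 = 2.0%; 7 points gives 0.0049/0.1275 = 3.8%. Both spreads are assumptions. Simulation with 12 sites and 20,000 trials gave power of 79.9% unstratified and 80.4% stratified at 5 points, and 80.2% and 81.2% at 7 points.

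A second simulation used 40,000 trials per scenario, 976 per arm, 12 sites of assumed unequal size, and assumed spread on the log-odds scale:

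| Site SD (log-odds) | Approx. range of site control rates | Type I error, unstratified / stratified | Power, unstratified / stratified |
|---|---|---|---|
| 0 | 15% | 2.6% / 2.6% | 80.2% / 80.1% |
| 0.3 | 9–23% | 2.5% / 2.5% | 80.1% / 80.3% |
| 0.5 | 7–31% | 2.4% / 2.5% | 80.6% / 81.1% |
| 0.8 | 4–42% | 2.3% / 2.6% | 81.0% / 83.2% |

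Monte Carlo standard error is √(0.025×0.975/40,000) = 0.08 points for type I error and √(0.8×0.2/40,000) = 0.2 points for power. The unstratified interval becomes slightly conservative as spread grows. The largest gain, about 2 points, needs very wide site differences.

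**4. What covariates could add.** If site plus baseline covariates explain 5% or 10% of outcome variance (an assumption with no figure in the article behind it):
- 5%: SE = 0.01605×√0.95 = 0.01565; power = Φ(0.045/0.01565 − 1.960) = 82.0%; equivalent extra participants 1952/0.95 − 1952 = 103.
- 10%: SE = 0.01605×√0.90 = 0.01523; power = Φ(0.045/0.01523 − 1.960) = 84.0%; equivalent extra participants 1952/0.90 − 1952 = 217.

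**The case against.** The best defence is that this is a condensed article. The interval method, pooling of small sites, model form and covariate list usually belong in the analysis plan, which is not shown. The article never calls its analysis unstratified; that is inferred from a plainly named test and interval. The effect is small and in the safe direction, and the planned power is reached without a site term. All of this stands, and it limits the point to efficiency and pre-specification. It does not remove the point, because the imbalance trigger is a stated rule and not a gap.

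A reader might infer three stronger criticisms, none of which the article supports:

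- *That a chi-square test of equality decides non-inferiority.* It does not. The same section gives the primary outcome its own confidence-interval rule against the 5-point margin.
- *That the trigger makes the final estimate depend on the data.* The adjusted analysis is described as a further one, which reads as supplementary. Nothing says it replaces the interval rule, although stating which result governs would settle the matter.
- *That an odds ratio will be compared with a margin in percentage points.* The article names no model and no effect scale for the multivariable analysis.

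**Conclusion.** The point holds as a modest improvement. Randomization is stratified by site, the analysis as stated does not use site, and adjustment depends on an imbalance that is chance under correct randomization.

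The 2.7% per covariate follows from the planned arm size; the 24% also assumes 10 independent covariates. Leaving out site costs about 0 to 2 points of power, according to the assumed site spread, with type I error staying near 2.5%. The rise to 82–84% power rests wholly on the assumed 5–10% of variance explained and should not be promised. No bias, no type I error inflation and no error in the sample size has been shown.

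**What to change.** 1. Keep the stated decision rule, but compute the one-sided 97.5% limit from a site-stratified risk difference (for example Mantel-Haenszel). Set a rule in advance for pooling very small sites.
2. Drop the 0.1 trigger. Pre-specify one supportive covariate-adjusted risk difference, for example by standardization from a logistic model so that it stays on the percentage-point scale, and fit it whatever the observed imbalance.
3. Fix its covariates now: site plus prognostic baseline variables. Candidates are disease type, disease duration and prior biologic exposure (the planned subgroup factors) and primary sclerosing cholangitis and disease extent (from Study eligibility). The Background also names prior colorectal neoplasia and active inflammation as risk factors. Check each against the case report form, which is in Additional file 1 and not shown here.
4. State that the site-stratified result decides non-inferiority and that the adjusted result is supportive.

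The cost is wording and minor programming, with no extra participants and no new data if the covariates are on the case report form. Trial management keeps allocation from investigators until the final analysis, so the change can be made before they see results by arm. If the unseen analysis plan already says this, the published text only needs to agree with it.

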The proposed non-inferiority margin of 5% is based on a large meta-analysis of 14 surveillance cohort studies in 671 patients with colonic IBD diagnosed with low-grade neoplasia (LGN) by either non-targeted or targeted biopsies, which calculated a pooled rate of progression of LGN to CRC of 0.8% per year [52]. Based on this estimate, if one-third of persons with LGN were missed in our intervention group relative to our reference group (i.e. reduction in absolute neoplasia detection rate from 15 to 10%), it would result in a theoretical 0.04% increased risk per year of CRC in our intervention group or 1 in 500 persons over 5 years. The steering committee and content experts deemed this to be an acceptable upper limit for a reduction in the neoplasia detection rate for the trial, given the potential for reduced procedural risks and costs with avoidance of non-targeted biopsies. This estimate also aligns with the only other RCT on this topic, in which investigators used a non-inferiority margin equivalent to roughly one-third of the baseline neoplasia detection rate [28].

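### The non-inferiority rule centres its confidence interval on the planning assumption of 0.5% instead of the observed difference, so read literally it cannot fail at the planned size

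*Protocol article*

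**What the plan says.** The decision rule for the primary outcome (the proportion of persons with at least one neoplastic focus) is in the Data analysis section. It relies on an interval described as a "one-sided 97.5% confidence interval around the expected true difference of 0.5% in favour of the control group (15% vs 14.5" per cent). Non-inferiority is shown when the upper bound of this interval rules out a deficit above 5%.

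The Sample size calculation section shows where these figures come from. The trial is sized "based on a 1-sided significance level of 2.5% and 80% power". The calculation proceeds by "assuming neoplasia detection rates of 15% and 14.5% in our control and intervention groups, respectively", with "a non-inferiority margin of 5" per cent, and gives 976 per group and 1952 in total. The 0.5-point gap is explained there as the authors' estimate, drawn from pooled literature and adjusted downwards. The margin is on the absolute scale: it is justified by the consequences of a "reduction in absolute neoplasia detection rate from 15 to 10" per cent.

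The article does not restate the rule for the observed difference anywhere. The chi-square test named in the same section for binary outcomes tests for a difference and gives no non-inferiority criterion.

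**The concern.** A non-inferiority conclusion has to rest on an interval around the difference that the trial observes. The sentence names a different centre, the expected true difference, and repeats the assumed pair of rates to identify it. So the text is not merely silent on the centre; it specifies the wrong one.

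Under the literal rule the observed difference has no part in the decision. Data can enter only through the standard error, and at the planned size that is never large enough to matter. The margin is argued from the later cancer risk of missed neoplasia, and the Ethics and dissemination section expects the results to influence guidelines. The sentence that decides the trial should therefore be usable as written.

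**Working it through.** **Inputs** (Sample size calculation section): control 15%, intervention 14.5%, margin 5 points, one-sided 2.5%, power 80%, 976 per group. Wald limits without continuity correction are assumed, because the article names no interval method.

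**1. Reproduce the sample size.**
- Variance term: 0.15 × 0.85 + 0.145 × 0.855 = 0.1275 + 0.1240 = 0.2515.
- Distance from the assumed difference to the margin: 0.05 − 0.005 = 0.045.
- n per group = 0.2515 × (1.960 + 0.842)² / 0.045² = 974.7, so 975 against the stated 976. Power at 976 is 80.05%.

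The sample size is sound, and its formula presumes a test based on the observed difference.

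**2. The rule as written, at the planned rates.**
- SE = √(0.2515 / 976) = 1.605 points.
- Upper limit = 0.5 + 1.96 × 1.605 = 3.65%, below 5% before any patient is enrolled.

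**3. The rule as written, with the SE from observed rates and the centre held at 0.5%.**
- The largest possible SE, with both rates at 50%, is √(0.5 / 976) = 2.263 points, giving 0.5 + 1.96 × 2.263 = 4.94%.
- With equal rates p, failure needs an SE above 4.5 / 1.96 = 2.296 points, that is p(1 − p) > 0.257. The maximum of p(1 − p) is 0.25, so failure is impossible.

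**4. Upper limits under the two readings** (976 per group, SE from the rates shown):

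| Observed control vs intervention | Centre fixed at 0.5% | Centre at observed difference |
|---|---|---|
| 15% vs 14.5% | 3.65% (pass) | 3.65% (pass) |
| 15% vs 13% | 3.58% (pass) | 5.08% (fail) |
| 15% vs 10% | 3.43% (pass) | 7.93% (fail) |
| 15% vs 5% | 3.12% (pass) | 12.62% (fail) |

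**5. Probability of declaring non-inferiority** (400,000 simulated trials per row, 976 per group, true control rate 15%):

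| True intervention rate | Centre fixed at 0.5% | Centre at observed difference |
|---|---|---|
| 14.5% | 100% | 80.0% |
| 13.5% | 100% | 60.0% |
| 12% | 100% | 25.3% |
| 10% (at the margin) | 100% | 2.6% |

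Only the right-hand column matches the planned power and significance level.

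**6. What the corrected rule demands.** With 15% observed in the control group, try an intervention rate of 13.1%: SE = √((0.1275 + 0.1138) / 976) = 1.57 points, and 1.9 + 1.96 × 1.57 = 4.98%, a pass. At a deficit of 1.92 points the limit reaches 5%. The largest passing deficit is therefore about 1.9 points.

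**7. Dependence on size.** With the centre fixed at 0.5%, the limit can reach 5% only when n per group falls below 0.2515 × 1.96² / 0.045², about 478, at the planned rates, or below 0.5 × 1.96² / 0.045², about 949, at rates of 50%.

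**The case against.** The best defence is that nobody would run the analysis this way. A confidence interval is computed from data, the section says that it concerns the full trial results, and the margin is argued as a limit on a real loss of detection. The stated power and significance level would be meaningless under the literal rule. The natural explanation is that the planning difference slipped into the analysis sentence. The article also condenses a fuller protocol, which may word the rule correctly.

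Most of this stands, and it limits what can be claimed. A reader might infer that the trial is built so that it must succeed, or that a large loss of detection would in practice be reported as non-inferior. The documents do not support that: the sample size, level and margin all point to an analysis of the observed difference. The defence does not rescue the sentence, however. This is an explicit misstatement, not a detail left for later, and an analysis plan that copied it would inherit the error.

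A reader might also object that the section says "The full trial results will be assessed by per-protocol analysis and intent-to-treat (ITT) analyses" without naming the set that governs the conclusion. That choice is commonly left to the statistical analysis plan, and nothing in the article contradicts itself on it. Requiring both sets to pass is one convention among several. It is not part of this point.

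**Conclusion.** The point holds as a wording error in the only success criterion stated for the primary outcome. As written, the rule returns non-inferiority whatever the trial observes at 976 per group, so its type I error at the margin is 100% against the planned 2.5%. The observed-difference reading recovers 80.0% power and a 2.6% pass rate at the margin, so the intended rule is hardly in doubt.

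The statement that the rule cannot fail rests on 976 per group and Wald limits. A smaller analysed set or another interval method could move the 4.94% ceiling past 5%, but that ceiling applies only at rates near 50%. At the planned rates the limit is 1.35 points clear of the margin. The sample size, the margin and its scale are not in question here.

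**What to change.** Replace the decision sentence in the Data analysis section with: *Non-inferiority will be declared if the upper limit of the one-sided 97.5% confidence interval for the observed difference in proportions (control minus intervention) is below 5 percentage points.* Keep the 15% and 14.5% figures in the Sample size calculation section only, and carry the same wording into the statistical analysis plan.

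The cost is one sentence. Sample size, power, significance level and margin are unchanged.
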